## Abstract

**Background:**

Postoperative hernias are a common and significant late complication following emergency abdominal surgery. Despite numerous preventive strategies, their incidence remains high, leading to morbidity, reoperations, and reduced quality of life. The PROPHECY trial is designed to assess the incidence of postoperative hernias and identify modifiable perioperative risk factors in patients undergoing urgent and emergency abdominal operations.

**Methods:**

This national, prospective, multicentre, observational cohort study will include adult patients undergoing emergency abdominal surgery for specific indications such as acute appendicitis, cholecystitis, incarcerated hernias, gastrointestinal perforation, or bowel obstruction. The study period extends from 1 June 2025 to 31 December 2026, with recruitment completed by the end of 2025 and follow-up completed by the end of 2026. Data on demographics, comorbidities, surgical techniques, postoperative management, and complication rates will be collected. The primary endpoints are incisional hernia, port-site hernia, and parastomal hernia. Secondary endpoints include surgical site infections (SSI) and burst abdomen. Follow-up will be conducted via structured telephone interviews and clinical or imaging confirmation. Based on power calculations for primary and secondary outcomes, the study will include 500 patients, providing adequate statistical strength while maintaining feasibility across participating centres.

**Trial registration:**

ClinicalTrials.gov ID: NCT06815822.

## Introduction

Emergency abdominal surgery is associated with increased rates of early and late postoperative complications, particularly the development of postoperative abdominal wall hernias [1]. This study protocol outlines the rationale and design of the PROPHECY trial, which will investigate this issue prospectively. Midline incisional hernias are among the most common complications after laparotomy and are associated with reduced quality of life, chronic pain, and need for complex reoperations [2, 3]. Despite a large number of analyzes on ways to reduce the incidence of this complication, it is still an important surgical problem [2]. Studies encompassing both elective and emergency procedures report postoperative hernia rates ranging from 2% to 40% [4]. This variation may be attributable to the often asymptomatic nature of certain hernias. An example are port-site hernias although generally perceived as rare, may occur more frequently than previously recognised, especially at umbilical sites [5]. Another significant surgical problem is parastomal hernias, occurring in up to 50% of patients with stomas [6]. The variability in reported incidence is also influenced by the method and duration of follow-up. True incidence rates are likely underreported, particularly in emergency surgery patients, where postoperative follow-up is frequently inconsistent or lacking.

Numerous studies and guidelines have investigated factors influencing hernia formation. Patient-related risk factors include diabetes, obesity, chronic pulmonary disease, immunosuppression, and a history of abdominal surgeries [7]. The guidelines of the European Hernia Society emphasize the need for further research into methods of preventing the occurrence of postoperative hernias [2]. Procedure-related factors such as the type of incision, suture material, fascial closure technique, and use of surgical drains also play a role in hernia pathophysiology [1, 4, 8]. The World Society of Emergency Surgery (WSES) and European Hernia Society (EHS) guidelines recommend the “small bites” technique for fascial closure using slowly absorbable sutures, although most of the supporting evidence is derived from elective surgery [1, 9]. Despite these recommendations, high-quality prospective data focusing exclusively on emergency surgery settings are limited. These guidelines highlight the importance of conducting prospective studies to establish the efficacy of this technique in urgent and emergency surgical procedures [1].

Management of surgical wounds and abdominal wall closure in the emergency setting remains highly variable, with limited evidence guiding best practice. Surgical site infection—affecting approximately one-third of patients undergoing emergency procedures—is also a well-established risk factor for postoperative hernia development [2, 7] A less common but clinically significant complication, which also contributes to hernia formation, is wound dehiscence or evisceration [10]. Therefore, prevention of such early postoperative complications is crucial in reducing the risk of subsequent hernia formation. Furthermore, there is a lack of consensus regarding the effectiveness of postoperative interventions aimed at hernia prevention, such as the use of abdominal binders or recommendations concerning the timing of return to full physical activity [9].

Given the substantial clinical burden posed by postoperative hernias and the paucity of targeted data in emergency surgery, the PROPHECY trial aims to quantify hernia incidence and assess modifiable perioperative risk factors within this high-risk cohort.

## Main and Secondary Hypotheses

### Primary Hypothesis

The incidence of postoperative hernias (incisional, port-site, and parastomal) in patients undergoing emergency abdominal surgery is high and is associated with modifiable perioperative risk factors.

### Secondary Hypotheses

• Specific surgical techniques, including fascial closure using the “small bites” method and slowly absorbable sutures, are associated with a lower incidence of postoperative hernia.
• Postoperative management strategies, such as the use of abdominal binders, NPWT, and early mobilisation, may reduce hernia occurrence.
• Infection of the surgical site (SSI) and burst abdomen significantly increase the risk of postoperative hernia formation.

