### Sample Size Justification

To estimate a 5% precision for postoperative hernia incidence with 95% CI, a minimum of 255 cases is required. For port-site hernias, at least 188 patients are required; for parastomal hernias, 349. For secondary outcomes, the required sample sizes are 255 for SSI and 93 for burst abdomen. Sample size considerations are summarised in Table 1. To detect a moderate effect size (Cohen’s d = 0.3) with 80% power at α = 0.05, the required sample size is.
• Chi-squared test (1 df): 88 patients
• Chi-squared test (5 df): 143 patients
• Student’s t-test: 102 patients

**TABLE 1 T1:** Sample size rationale.

Endpoint	Sample size	Notes
Incisional Hernia	255	To estimate with 5% precision, 95% CI
Port-site Hernia	188	To estimate with 5% precision, 95% CI
Parastomal Hernia	349	To estimate with 5% precision, 95% CI
Surgical Site Infection (SSI)	255	To detect moderate effect size, 80% power
Burst Abdomen	93	To detect moderate effect size, 80% power

The total planned cohort will consist of 500 patients, which ensures sufficient power to assess primary and secondary outcomes while allowing for exploratory and subgroup analyses, including risk factors associated with specific surgical techniques or patient characteristics. This sample size also accommodates a potential dropout rate of up to 10% and supports the development of multivariate models with adequate statistical reliability.

To ensure feasibility across all participating centres, over-recruitment will be limited to a maximum of 50% above the calculated minimum sample size required for primary endpoints.

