Parastomal hernias remain another prevalent but under-reported complication. A study by Antoniou et al. found that up to half of patients with permanent stomas develop a hernia at the stoma site [6]. Evidence supports the use of prophylactic mesh in elective stoma formation to reduce this risk [6, 13], but the safety and feasibility of mesh use in emergency stoma creation is still debated due to concerns regarding infection. A meta-analysis by Elzeftawy et al. demonstrated that mesh implantation—particularly in the retromuscular position—significantly reduces the risk of parastomal hernia without increasing the incidence of surgical site infections [13].

One of the most important modifiable factors identified in the literature is surgical site infection (SSI), which significantly increases the risk of incisional hernia development [7, 12]. The use of prophylactic negative pressure wound therapy (NPWT) on closed incisions has shown promise in reducing SSI rates, particularly in high-risk or contaminated fields [14]. Nevertheless, adoption of NPWT in emergency settings remains inconsistent. PROPHECY will capture detailed data on the use of NPWT and its association with hernia and wound-related outcomes.

The inclusion of burst abdomen as a secondary endpoint reflects the growing awareness of this severe complication. Kvist et al. recently reported that burst abdomen following emergency laparotomy occurred in 4.4% of patients and was associated with significantly higher rates of morbidity and mortality [10]. This underlines the importance of optimal fascial closure and early identification of wound dehiscence in this population.

Another area of interest is postoperative care, including the use of abdominal binders and guidance on physical activity resumption. While widely practised, there is limited high-quality evidence supporting their role in preventing hernia formation [2, 9]. PROPHECY will contribute to clarifying the effectiveness of these interventions.

Finally, the multicentre, prospective design and robust sample size calculation of the PROPHECY trial will allow for meaningful subgroup analyses and generalisable conclusions.

By identifying both patient- and procedure-related modifiable risk factors, this study has the potential to inform the creation of specific guidelines for hernia prevention in emergency surgery, where currently none exist.

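### The stated power does not carry over to burst abdomen as a risk factor for hernia: about 20 to 30 exposed patients give well under 80% power for a doubling of risk unless the baseline hernia risk is high

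*Protocol article*

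**What the plan says.** The third secondary hypothesis in the protocol article reads "Infection of the surgical site (SSI) and burst abdomen significantly increase the risk of postoperative hernia formation". Burst abdomen is thus an exposure and hernia the outcome, although burst abdomen is also listed as a secondary endpoint.

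Under Statistical Analysis, categorical variables are compared by chi-squared at p < 0.05, logistic regression is used for risk factors, and relative risks are given with 95% confidence intervals.

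Under Sample Size Justification the article says "The total planned cohort will consist of 500 patients, which ensures sufficient power to assess primary and secondary outcomes". It allows for up to 10% dropout and gives chi-squared sample sizes of 88 (1 df) and 143 (5 df) for an effect size of 0.3 with 80% power. For the secondary outcomes, "the required sample sizes are 255 for SSI and 93 for burst abdomen". The text places these two figures directly after the precision calculations, while Table 1 labels both as sized for power to detect a moderate effect.

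The only burst abdomen rate in the article is in the Discussion, where a cited study is reported to have found that "burst abdomen following emergency laparotomy occurred in 4.4% of patients".

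**The concern.** When a rare event is the exposure, the information about its effect comes mainly from the small exposed group, not from the total of 500. None of the association calculations uses an exposure prevalence or a hernia rate. A reader would take the power sentence and the Table 1 label to cover the burst abdomen hypothesis, when the design may have too few exposed patients to detect even a doubling of hernia risk.

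At stake is how the result is read. A non-significant finding from a study described as adequately powered could be mistaken for evidence of no association. A significant finding obtained at low power tends to come with an exaggerated estimate.

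**Working it through.** **Inputs from the article.** 500 patients; up to 10% dropout, so 450 evaluable; burst abdomen 4.4% after emergency laparotomy (Discussion); effect size 0.3, 80% power, α = 0.05 (taken as two-sided); chi-squared test.

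**Assumed inputs.** The article gives no relative risk for burst abdomen and no planning hernia rate. I take RR = 2 and an unexposed hernia risk of 10% to 30%, within the 2% to 40% quoted in the Introduction. I also assume that all exposed patients can be assessed at 12 months.

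**1. The plan's own figures.** Noncentral chi-squared with w = 0.3 gives N = 87.2, so 88 (1 df), and 142.5, so 143 (5 df). Both reproduce, with 0.3 acting as Cohen's w.

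The 93 for burst abdomen fits the precision formula 1.96² × p(1 − p)/0.05² at p of about 6.5%: 3.8416 × 0.0647 × 0.9353/0.0025 = 93. In the same way 255 fits p of about 21%. The article states neither rate, so both are inferences.

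**2. What w = 0.3 means for a rare exposure.** For a 2×2 table, w = d × √[e(1 − e)] / √[p̄(1 − p̄)], where e is the share exposed, d the risk difference and p̄ the overall hernia risk.
- With e = 0.044 and p̄ = 0.21, w = 0.3 requires d = 0.3 × √(0.21 × 0.79)/√(0.044 × 0.956) = 0.60. Solving with the unexposed risk fixed at 20% gives 0.61.
- A doubling from 20% to 40% gives p̄ = 0.2088 and w = 0.2 × √(0.044 × 0.956)/√(0.2088 × 0.7912) = 0.101. The N for 80% power is 7.849/w², about 770.

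**3. Number exposed.** 450 × 0.044 = 19.8, about 20; without dropout, 500 × 0.044 = 22. At 6.45%, 450 × 0.0645 = 29. Applying either rate to everyone treats every operation as open.

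**4. Power for RR = 2**, two-sided 0.05, by exact enumeration of both binomials (Fisher to uncorrected chi-squared):

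| Unexposed hernia risk | 20 vs 430 | 29 vs 421 |
|---|---|---|
| 10% | 28–33% | 35–41% |
| 20% | 51–56% | 64–69% |
| 30% | 76–80% | 89–91% |

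By the normal approximation, 80% power is reached at an unexposed risk of about 30% with 20 exposed and about 25% with 29.

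**5. Detectable effect with 20 exposed.** The relative risk for 80% power is about 3.3 at a 10% risk, 2.7 at 15% and 2.4 at 20% (normal approximation). At 20% and RR 2.4, exact power is 77% (Fisher) to 80% (chi-squared).

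**6. If only part of the cohort is open.** The eligible indications include appendicitis and cholecystitis, and the surgical approach (open or minimally invasive) is a recorded variable. The open share is not given. If it were half and the analysis were restricted to open cases (10 vs 215), power for RR = 2 would be about 23% at a 10% risk and 36% at 20% (normal approximation).

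**7. Surgical site infection, for contrast.** The Introduction puts it at about one-third of emergency patients. With 150 exposed of 450, power for RR = 2 is about 82% at a 10% risk and 95% at 15%.

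**The case against.** Several points on the other side have force.

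- **The 4.4% is not a planning rate.** It is another study's result, and the one sizing figure for burst abdomen suggests about 6.5% if read as precision. A reader might infer that the plan can yield no more than 20 exposed patients; the article does not support that as a ceiling. The higher rate still leaves power at 64–69% for a doubling from 20%.
- **Any single power figure is conditional.** A reader might summarise power as about 50%. That needs RR = 2 and an unexposed risk near 17% (normal approximation) or 20% (Fisher), and the article fixes neither. With RR = 2.5 at a 20% risk, exact power with 20 exposed is 82–85%, so large effects are not out of reach.
- **The 255 is not an expected number of open operations.** It is a precision size and cannot be used to count exposed patients.
- **The power sentence may not be meant for this contrast.** Burst abdomen is a secondary outcome to be reported as a proportion, and the same sentence mentions risk factors among exploratory and subgroup analyses. So a flat contradiction is not established. But the hypothesis itself speaks of a significant increase, and Table 1 attaches 80% power for an effect to burst abdomen, so the reader is led to connect them.
- **Part of the remedy already exists.** Relative risks with 95% intervals are planned, and they would show the imprecision. The choice of an exact test for small cells can be left to the analysis plan.

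These points limit the size and certainty of the finding. They do not make the effect size of 0.3 applicable to so rare an exposure.

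**Conclusion.** The point holds in conditional form. The stated power does not describe the test of burst abdomen as a risk factor for hernia. For a doubling of risk, power is roughly 28–41% at a 10% unexposed hernia risk and 51–69% at 20%, across 20 to 29 exposed patients. It reaches 80% only at an unexposed risk of about 25–30%. These figures rest on RR = 2, on rates of 4.4% to 6.5% applied to all 450 evaluable patients, and on full assessment of the exposed; laparoscopic cases or losses among the exposed would lower them.

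A reader might go further and infer that the hypothesis cannot be tested or must be dropped, or that a non-significant result would refute it. The documents do not support this: relative risks of about 2.4 and above are detectable at a 20% risk, and a non-significant result would be inconclusive. Nor does the point extend to surgical site infection. It concerns one half of one secondary hypothesis in an observational study.

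**What to change.** Make these wording changes in Sample Size Justification, Table 1 and Secondary Hypotheses:

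- Limit the power sentence so that it does not cover burst abdomen as a risk factor for hernia. Correct the Table 1 label for burst abdomen to say what the 93 was calculated for and at which assumed rate.
- State the expected number of patients with burst abdomen (about 20 to 30, fewer if many operations are laparoscopic) and the relative risk detectable with that number at a stated hernia risk.
- Mark the burst abdomen half of the hypothesis as exploratory. Report hernia after burst abdomen as a proportion and a relative risk with an exact 95% confidence interval, and say in advance that a non-significant result will be read as inconclusive.
- Leave the surgical site infection half unchanged.

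No additional patients or data are needed. The cost is a less favourable power statement for one half of one secondary hypothesis. Removing the significance test altogether is a possible preference but is not required.

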## Methods and Design

### Study Design and Registration

The PROPHECY trial is a prospective, multicentre, observational cohort study conducted across multiple surgical centres in Poland. The study will run from June 2025 to December 2026, with follow-up and final data analysis planned for early 2027. It is coordinated by the Department of Surgical Sciences and the Laboratory of Medical Genetics of the Medical College, Jan Kochanowski University in Kielce, Poland. Ethical approval was granted by the Institutional Bioethics Committee (Decision No. 5/2025), and the study is registered at ClinicalTrials.gov (NCT06815822). This protocol is published prior to patient enrolment in order to enhance methodological transparency, facilitate reproducibility, and reduce the risk of selective reporting.

### Study Timeline

• Centre enrolment: May 2025• Patient recruitment: 1 June 2025–31 December 2025• Follow-up period: 1 January 2026–31 December 2026• Data analysis: January 2027• Expected publication: February/March 2027

### Eligibility Criteria

#### Inclusion Criteria

• Age ≥18 years
• Undergoing emergency abdominal surgery for one of the following indications:▪ Acute appendicitis▪ Acute cholecystitis▪ Incarcerated abdominal hernia▪ Gastrointestinal perforation▪ Bowel obstruction

#### Exclusion Criteria

• Patient refusal to participate
• Open abdomen technique utilised intraoperatively

### Data Collection

Clinical and demographic variables to be collected include age, sex, body mass index (BMI), comorbidities, ASA (American Society of Anesthesiologists) classification, and history of prior abdominal surgery. Perioperative variables include the type of surgical approach (open vs. minimally invasive), operative technique, use of drains, irrigation or lavage of the wound, fascial closure method (technique and material), and wound management strategies including NPWT. Postoperative variables such as the use of abdominal binders or elastic taping and time to full physical activity resumption will also be recorded.

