### Follow-Up Protocol

All participants will be followed up 12 months after discharge via telephone by a trained physician using a structured interview. In cases of suspected hernia, patients will be invited for outpatient clinical examination and ultrasound or CT imaging to confirm the diagnosis.

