### Statistical Analysis

The primary and secondary outcomes will be expressed as proportions with 95% confidence intervals. Continuous variables will be described using medians and interquartile ranges and analysed using Student’s t-test or the Wilcoxon test as appropriate. Categorical variables will be compared using the Chi-squared test. Univariate and multivariate logistic regression models will be applied to identify independent risk factors for postoperative hernia formation. Relative risk (RR) with 95% CI will be calculated. A p-value <0.05 will be considered statistically significant. All analyses will be conducted using R software in RStudio.

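### Binder use and time to full activity are not fixed before hernia onset, so their associations with hernia are open to reverse causation

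*Protocol article*

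**What the plan says.** All places are in the Protocol article.

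- **Secondary Hypotheses:** "Postoperative management strategies, such as the use of abdominal binders, NPWT, and early mobilisation, may reduce hernia occurrence".
- **Data Collection:** "Postoperative variables such as the use of abdominal binders or elastic taping and time to full physical activity resumption will also be recorded". NPWT appears separately, with the perioperative items, under "wound management strategies including NPWT".
- **Follow-Up Protocol:** "All participants will be followed up 12 months after discharge via telephone by a trained physician using a structured interview". Then: "In cases of suspected hernia, patients will be invited for outpatient clinical examination and ultrasound or CT imaging to confirm the diagnosis". No other contact after discharge is described.
- **Statistical Analysis:** "Univariate and multivariate logistic regression models will be applied to identify independent risk factors for postoperative hernia formation". Continuous variables go to a t-test or Wilcoxon test and categorical ones to a chi-squared test, and "A p-value <0.05 will be considered statistically significant".
- **Discussion:** the study is expected to help clarify how effective binders and guidance on resuming activity are.

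**The concern.** To count as a risk factor for hernia, an exposure has to be settled before the hernia appears. Nothing in the article secures this for binder or taping use or for time to full activity. Full activity is normally regained some time after discharge, and the one later contact described is the call at which hernia is first suspected. A patient with a painful or bulging wound may go back to full activity later, or may start wearing a binder because of it.

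The two biases pull in different directions:

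- For activity, late return looks harmful and early return looks protective, which favours the hypothesis if time to full activity stands in for mobilisation.
- For binders, use looks harmful, or a real benefit is hidden.

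Adjusting for baseline covariates repairs neither. No later analysis plan can recover the time order if the dates were never collected. At stake are one secondary hypothesis and the effectiveness reading announced in the Discussion.

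A separate, smaller point is that Secondary Hypotheses names early mobilisation, while Data Collection names only time to full activity, a later and different quantity.

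**Working it through.** The plan gives no figure on this point to reproduce. The check is one of time order, followed by an illustration of size.

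**Time order**

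| Variable | When recorded, per the article | Can a hernia change it? |
|---|---|---|
| NPWT | Listed with perioperative variables | Largely not |
| Binder or taping | Not stated; discharge is possible | Yes, if later use counts |
| Time to full activity | Not stated; for most patients knowable only after discharge | Yes |

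The article mentions no hernia date, landmark or time-dependent covariate.

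**Illustration 1: time to full activity, no true effect**

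Inputs from the article:
- Sample size: "The total planned cohort will consist of 500 patients", less the 10% dropout allowed for, gives 500 × 0.9 = 450.
- Hernia risk 21%. This is the risk implied by the 255 patients stated for 5% precision: 1.96² × 0.21 × 0.79 / 0.05² ≈ 255.

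Assumed inputs, not in the article:
- Return time is lognormal with median 8 weeks and log-SD 0.5, independent of hernia.
- Onset is either uniform over 52 weeks or early (half-life 16 weeks, within 52 weeks).
- A hernia that precedes return delays it by 4 or 8 weeks in all, 50% or 25% of such patients.

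Rough scale: 450 × 0.21 = 94.5 hernias.
- Uniform onset puts about 94.5 × 8/52 ≈ 15 of them before week 8.
- Early onset puts about 94.5 × (1 − 2^(−8/16)) / (1 − 2^(−52/16)) = 94.5 × 0.293/0.895 ≈ 31 before week 8.

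Results from 1,000 to 2,000 simulated cohorts per setting. Each cell gives the OR for return after 8 weeks, where available, and the Wilcoxon rejection rate at 0.05:

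| Onset, delay | All delay | 50% delay | 25% delay |
|---|---|---|---|
| Uniform, 4 weeks | 1.22; 20% | 8% | 6% |
| Uniform, 8 weeks | 1.25; 35% | 1.12; 13% | 1.06; 7% |
| Early, 4 weeks | 1.57; 60% | – | – |
| Early, 8 weeks | 1.61; 89% | 1.27; 39% | 1.13; 14% |

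With no delay the OR is about 1.0 and rejection about 5%. Repeat runs differ by simulation error: the standard error at 35% with 1,000 cohorts is √(0.35 × 0.65/1000) ≈ 1.5 points. The OR and the rejection rate belong to different tests. For the OR of 1.25, a chi-squared test on the dichotomised variable rejects in about 15%.

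**Illustration 2: binders, no true effect, if use after onset is counted**

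Let b be baseline use and q the share of non-users with hernia who start a binder because of it. Use among hernia patients is p₁ = b + (1 − b)q, and OR = [p₁/(1 − p₁)] / [b/(1 − b)].

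- b = 0.2, q = 0.10: p₁ = 0.28, OR = (0.28/0.72)/(0.2/0.8) = 1.56.
- b = 0.4, q = 0.10: p₁ = 0.46, OR = (0.46/0.54)/(0.4/0.6) = 1.28.
- b = 0.2, q = 0.25: p₁ = 0.40, OR = 2.67.
- b = 0.4, q = 0.25: p₁ = 0.55, OR = 1.83.

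With 450 patients and hernia risk of 10% to 30%, the chi-squared false-positive rate (20,000 runs) is 13–46% at q = 0.10 and 49–99% at q = 0.25. At q = 0, for example with binder status fixed at discharge, the OR is 1.00 and the rate is about 5%. Here b, q and the hernia risk are all assumed.

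**The case against.** The strongest reply is that this is a condensed article. Exposure windows, case-form fields, interview questions and the choice of model covariates usually sit in documents not shown. That reply limits the point in several ways.

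- A reader might infer that both variables are recorded after the hernia. The text does not say so. For activity time it is a strong inference from the single later contact. For binders it is not established, because use could be entered during the index stay.
- A reader might infer that early mobilisation will not be collected. The Data Collection sentence is an open list, so the text shows only a mismatch of wording. That mismatch does not itself cause reverse causation.
- A reader might take the whole postoperative-care hypothesis to be compromised. NPWT is listed as perioperative, and mobilisation in the usual in-hospital sense comes before a hernia.
- A reader might take the largest simulated figures as typical. They require every hernia that precedes return to delay it. The Introduction itself notes that some hernias are often asymptomatic, and those need not delay anything.
- The article does not name the variables that will enter the models, and its language is cautious: the strategies may reduce hernia, and the study will contribute to clarification.

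The core still stands. The article sets out a hypothesis, the variables, one follow-up contact, methods without time order and an effectiveness aim. Followed as written, these allow a consequence of hernia to be reported as a cause. The remedy is a matter of data collection, so it cannot safely be left to the analysis stage.

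**Conclusion.** The concern holds for two variables: time to full activity and, if use after discharge is counted, binders or taping. Their associations with hernia cannot be read as effectiveness on the design described.

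For activity with no true effect, the plausible range is wide: an OR of about 1.05 to 1.6, and a Wilcoxon false-positive rate from about 5% (uniform onset, a quarter of early hernias delaying return) to about 90% (early onset, all delaying return). If only half or a quarter delay return, the OR is about 1.05 to 1.25 and the rate lies between about 5% and just under 40%. These figures rest on the assumed return times, onset patterns, delays and shares. The direction of the bias does not depend on the exact values, but its size does.

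The incidence endpoints and the NPWT comparison are largely unaffected. The change should be made, because it is cheap and the information is lost if it is not collected.

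**What to change.** 1. Enter three items on the case form at discharge: day of first mobilisation, binder or taping status, and the activity advice given. Use these as the exposures for the postoperative-care hypothesis.
2. At the existing 12-month call, ask when a hernia or bulge was first noticed.
3. Keep actual time to full activity descriptive. Alternatively, analyse it as resumed or not resumed at a fixed early landmark (for example 6 weeks), among patients with no hernia or bulge noticed before it.
4. Align the wording: either name early mobilisation in Data Collection or restate the hypothesis in terms of the activity variable collected.
5. If binder use after discharge is also recorded, give it start dates so that use begun after onset can be separated.

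The core change costs three form fields and one interview question, with no extra visit; item 5 adds a date field if that option is used. There are two limits. Status or advice at discharge is not the same as later behaviour, so the estimated effect is of what was started or advised. A date recalled at 12 months is also imprecise, so a landmark analysis would need a sensitivity check on the chosen time.
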